**ASP-HEARING STUDY PLAN**

**1. RECRUITMENT:** All newly enrolled ASPREE participants in 2014 will be invited at their baseline visit to enter ASP-HEARING, regardless of existing hearing impairment. Recruitment to

ASP-HEARING is during the final phase of ASPREE's recruitment in 2014, funded by Monash University, and it is anticipated that 1,800-2,100 of the remaining ASPREE trial recruits will consent to participate.

**2. HEARING MEASURES:** Hearing tests will be conducted without hearing aids. Any aids will be turned off and removed after testing instructions are heard and understood. Previously unknown hearing impairment will be advised to the participant's GP.

**2.1 OTOSCOPY** will be performed at the outset of the hearing evaluation. If the eardrum is occluded, the participant and their GP will be informed. Responsibility for management of any obstruction will rest with the GP. The participant will return for hearing reassessment following management of the obstruction, if this is initiated promptly within two months of randomisation.

**2.2 AUDIOMETRY AIR and BONE CONDUCTION TESTS:** In order to test the main hypothesis, hearing acuity will be tested at baseline and annually for the three years of ASP-HEARING. Pure Tone Audiometry: portable Interacoustics AD226 audiometers with ER3A inserts and sound-attenuating ear muffs, will be used to obtain air-conduction thresholds in both ears at standard octave frequencies (0.25, 0.5, 1, 2, 4, and 8 kHz). A pure tone average of air conduction thresholds at 0.5, 1, 2, and 4 kHz in the better ear will be the summary measure of hearing used in our analyses, as per the definition of hearing deficit used by the World Health Organization. (52) A bone conduction test will be performed on the better ear using two frequencies, 1 kHz and 4 kHz. This will enable distinction of age-associated sensorineural hearing loss from conductive loss – the latter irrelevant to this study. Audiometric equipment for baseline measures has been purchased with assistance from Monash University. Over the 3-year study period, even subtle changes in hearing threshold will be measureable in all participants, including any deterioration that is imposed on hearing impairment at baseline.

**2.3 SPEECH IN NOISE TEST:** The Listening in Spatialised Noise-Sentence Test (LiSN-S) (53) assesses the ability to understand speech in the presence of spatially-separated, competing talkers. A simple repetition response assesses a listener's speech reception threshold for target sentences within background noise. Speech discrimination is affected both by cochlear loss and by the presence of certain central auditory processing disorders, (54) and together with the pure tone results the LiSN-S will help this distinction to be made. This test will provide us with a vital measure of functional hearing, the Speech Reception Threshold in noise (SRTn).

**2.4 HEARING HANDICAP AND NOISE EXPOSURE QUESTIONNAIRES:** The 10 item Hearing Handicap Inventory for the Elderly (HHIE-S) (55) and the 11 item Baltimore Longitudinal Study of Aging Self-Reported Hearing and Noise Exposure Questionnaire (56) will be administered to provide information on hearing history, noise exposure, use of hearing aids and perceived hearing handicap. This will also assist in determining the extent to which previous noise exposure contributes to hearing thresholds.

**3. INFLAMMATORY BIOMARKERS:** To test subsidiary hypothesis 1, inflammatory biomarkers IL-6, CRP and TNF- $\alpha$  will be measured in blood samples taken at baseline and change in these biomarker levels will be determined from levels measured in 3-year bloods collected by the ASPREE Healthy Ageing Biobank.

**4. RETINAL VESSEL IMAGING (RVI):** To test subsidiary hypothesis 2, retinal photography will be used to measure retinal vessel diameters, branching and vessel wall opacity and tortuosity. We are seeking evidence of microvascular changes which may be a causal factor in presbycusis. RVI provides a convenient and accessible measure of blood vessel change. ASP-HEARING will take advantage of RVI equipment currently used by ASPREE's Age Related Macular Degeneration (AMD) sub-study.

**5. COGNITIVE FUNCTION TESTS:** To test subsidiary hypothesis 3, results from annual cognitive function assessments will allow determination of associations and causal relationships

through comparisons of changes over time (annually) in the key factors of hearing threshold, retinal vessel and cognition. ASP-HEARING will take advantage of the 3MS scores obtained by the parent trial, which are suitable measures of cognitive decline, to inform this hypothesis. Cognitive function is assessed at Years 0, 1, and 3 in the parent trial; therefore ASP-HEARING will require one additional single 3MS measure at Year 2 to complete the annual measures.

**TIMELINE:** ASP-HEARING commences recruitment in 2014.

*Unshaded boxes indicate measures not currently covered by ASPREE or other sub studies*

| ASP-HEARING STUDY                                                                                                                                                                                                                                                                                                                                                                                                                                 | 2014 | 2015 | 2016 | 2017 | 2018                                  |
|---------------------------------------------------------------------------------------------------------------------------------------------------------------------------------------------------------------------------------------------------------------------------------------------------------------------------------------------------------------------------------------------------------------------------------------------------|------|------|------|------|---------------------------------------|
| Audiometry a and Otoscopy                                                                                                                                                                                                                                                                                                                                                                                                              | X    | X    | X    | X    | Data
Analysis
Papers
Reports |
| Hearing Questionnaires b                                                                                                                                                                                                                                                                                                                                                                                                               | X    | X    | X    | X    |                                       |
| Retinal Vascular Imaging                                                                                                                                                                                                                                                                                                                                                                                                                          | X    | X    | X    | X    |                                       |
| Cognitive Function Tests c                                                                                                                                                                                                                                                                                                                                                                                                             | X    | X    | X    | X    |                                       |
| Inflammatory Biomarkers                                                                                                                                                                                                                                                                                                                                                                                                                           | X    |      |      | X    |                                       |
| ASPREE PARENT TRIAL                                                                                                                                                                                                                                                                                                                                                                                                                        |      |      |      |      |                                       |
| Cognitive Function Tests c                                                                                                                                                                                                                                                                                                                                                                                                             | X    | X    |      | X    |                                       |
| Demographics & Physical Measurements, d BP, Health Behaviours Cardiovascular Biomarkers, e Lifestyle f                                                                                                                                                                                                                                                                                                           | X    | X    | X    | X    |                                       |
| ASPREE RETINAL/BIOBANK SUB STUDIES                                                                                                                                                                                                                                                                                                                                                                                                         |      |      |      |      |                                       |
| Retinal Vascular Imaging                                                                                                                                                                                                                                                                                                                                                                                                                          | X    |      |      | X    |                                       |
| Inflammatory Biomarkers                                                                                                                                                                                                                                                                                                                                                                                                                           | X    |      |      | X    |                                       |
| Shading highlights data collection supported by the ASPREE trial                                                                                                                                                                                                                                                                                                                                                                                  |      |      |      |      |                                       |
| a Pure Tone Audiometry air conduction & bone conduction; LISN-STEST b HHIE-S & BLSA;
c 3MS, HVLT-Revised, COWAT-F, SDMT; d First language, education, family history, co-morbidity, height, weight, waist; e Cholesterol, LDL-C, HDL-C, triglycerides, Hb, gluc. creatinine, urine albumin:creatinine ratio; f Physical activity, smoking history & alcohol use; SF-12, IADL |      |      |      |      |                                       |

**POWER AND SAMPLE SIZE CALCULATIONS:** To address the primary hypothesis, 1800 participants provide 80% power to detect a difference in average hearing level/threshold (HL) change from a mean annual dB HL increase of +0.86 in the placebo group to a mean annual dB HL increase of +0.64 in the aspirin group (assuming SD of 1.64 dB HL for changes in HL over 3 years). This calculation is based on the background increase per annum of HL in Australians aged ≥75, with an average Pure Tone Audiometry 0.5, 1, 2, 4 kHz trajectory of +0.86 dB.(8)

**STATISTICAL ANALYSIS:** A linear mixed model with HL at years 0, 1, 2, and 3 as the repeatedly measured outcome will be used for all analyses equivalent to a model for follow-up HL measures that adjusts for baseline HL. (57) For the main hypothesis, the model will include an interaction term between treatment group (placebo/aspirin) and time since randomisation; the estimated interaction effect will summarise the evidence for/against this hypothesis. This model assumes a missing at random (MAR) mechanism for any unobserved HL values. Secondary analyses will include a sensitivity analysis of findings to the MAR assumption, enabling exploration of whether differential drop-out between groups during the follow-up period affects the estimates of treatment effect.

The same model structure will be used to assess evidence for the subsidiary hypotheses. Separate analyses will be undertaken for the inflammatory biomarkers: TNF- $\alpha$ , IL-6 and CRP, for the retinal microvascular change indicators (retinal arteriolar, venular calibre and focal arteriolar narrowing), and for cognitive impairment as measured by 3MS noting that each of these measures is on a continuous scale. For example, for TNF- $\alpha$ , the model will be extended to include the baseline TNF- $\alpha$  values and its corresponding parameters relating it to HL at baseline will assess evidence for cross-sectional association at baseline. For assessing association of biomarker changes with progression of HL, the model will be further extended to include the time-dependent TNF- $\alpha$  change from baseline as an explanatory variable. For assessing whether TNF- $\alpha$  mediates an aspirin-induced

slowing of HL, the model will be extended again to include an interaction between treatment group (placebo/aspirin) and the time-dependent TNF- $\alpha$  change from baseline.

**ETHICS:** Written informed consent will be obtained from all ASP-HEARING participants. ASPREE has ethical approval from the Human Research Ethics Committees of Monash University, the Royal Australian College of General Practitioners, University of Tasmania, University of Adelaide, Australian National University and ACT Health. ASP-HEARING will seek additional ethical approval.

**FEASIBILITY:** The feasibility of ASP-HEARING is assured by the following:

1. The ASPREE trial has funding secured from both an NHMRC seed grant and the NIH (\$US50m) and the ASPREE Healthy Ageing Biobank has been funded by the CSIRO and the National Cancer Institute (USA).
2. Recruitment processes are established with successful recruitment of 13,700 participants into ASPREE to date, with recruitment of the remaining 2,800 participants continuing until late 2014, enabling ASP-HEARING to enrol and follow-up the necessary numbers of participants.
3. Other ancillary studies to ASPREE successfully utilise Retinal Vascular Imaging techniques (ENVISion and SNORE-ASA), and have proved attractive to ASPREE participants.
4. The CI-A is CI-A on SNORE-ASA, CIB on ENVISion, and a named investigator on ASPREE; AI [name] is the Principal Investigator of ASPREE; CI [name], CI [name] and AI [name] are named investigators; and CI [name] is the Executive Officer of ASPREE – providing a pivotal link that ensures smooth implementation of ASP-HEARING.
5. ASP-HEARING will extend collaborations with the National Acoustic Laboratory, The HEARING Cochlear Research Centre, Johns Hopkins University and RUSH University – USA.
6. CI [name], CI [name] and CI [name] are internationally recognised experts in hearing research.
7. Many investigators for this proposal have long-standing successful collaborations including previous NHMRC-funded studies.
8. Significant cost benefits are filtered to ASP-HEARING from ASPREE. Access to all currently funded elements estimated savings of \$640 per recruitment and \$300 per annual visit.
9. Retinal cameras in ASPREE clinics and installed in specially outfitted clinic vehicles are available for use in this study, funded by another NHMRC sub-study of ASPREE focused on age-related macular degeneration and from philanthropic donations.
10. ASPREE has achieved recruitment success across metropolitan and regional areas of 4 States in south-eastern Australia by taking study staff and laboratories to the people. A primary prevention trial of this magnitude and complexity in community-dwelling older people would not be feasible without the research infrastructure developed for ASPREE; based primarily in general practices supported by customized research vehicles. Please see Table 1. For elements of ASP-HEARING already funded by ASPREE and related sub studies.

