**Relationship to ASPREE trial**

ASPREE (ASpirin in Reducing Events in the Elderly) is a 5 year RCT comparing low-dose aspirin (daily slow release 100mg enteric coated) with placebo in 19,000 community-dwelling adults aged  $\geq 70$  years. The primary outcome is disability-free survival, in relation to physical disability and dementia. ASPREE participants are free of previous cardiovascular disease or stroke, dementia and other severe illness at trial entry. Although ASPREE has been funded by the US National Institutes of Health, the majority of the trial is in Australia with 16,500 participants and 2,500 in the US. At present, >13,700 Australian participants have been recruited. Recruitment will be completed by late 2014, with follow-up concluding by late 2017. Infrastructure, recruitment, data collection, follow-up and participant retention methods are well-established. Additional benefits for ASP-HEARING include access to comprehensive socio-demographic data, clinical history, significant clinical events (adjudicated endpoints), measures of activities of daily living, cognitive assessment, cardiovascular events, depression, other co-morbidities, medications and hospitalisations in the ASPREE cohort.

*Recruitment:* Participants are selected from general practices and undergo phone screening to assess suitability. Potential participants attend a baseline examination for testing and distribution of run-in (placebo) medication. Eligible participants attend further testing and are randomised to either aspirin or placebo at one month. The majority agree to provide blood and urine specimens which are stored for later biomarker and genetic analysis. ASPREE participants are telephoned regularly to support compliance. Evidence of major clinical events is collected from medical records and categorised by blinded outcomes committees.

*Inclusion criteria:* persons aged  $\geq 70$  years of age, who are English language competent, community dwelling, physically capable of regularly attending their GP, and providing informed consent.

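### The power statement gives the treatment difference per year but the SD per 3 years, and 1,800 for 80% power does not follow from the inputs as labelled

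*Protocol*

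**What the plan says.** The only power statement is in the Protocol, ASP-HEARING Study Plan, under Power and Sample Size Calculations. It says that "1800 participants provide 80% power" to distinguish "a mean annual dB HL increase of +0.86 in the placebo group" from "a mean annual dB HL increase of +0.64 in the aspirin group". The parenthesis that follows gives the variability: "assuming SD of 1.64 dB HL for changes in HL over 3 years". A source is cited for the placebo trajectory of 0.86 dB per year. None is cited for the SD. The paragraph gives no alpha, sidedness, allocation ratio or allowance for loss to follow-up, and no conversion between annual and 3-year quantities.

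On measurement, the Audiometry section says that "hearing acuity will be tested at baseline and annually for the three years of ASP-HEARING". The Statistical Analysis paragraph makes the treatment-by-time interaction in a linear mixed model, with visits at years 0, 1, 2 and 3, the estimate that answers the main hypothesis.

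**The concern.** A standardised effect needs its numerator and denominator on the same time scale. Here the numerator is 0.86 − 0.64 = 0.22 dB per year and the denominator is labelled as the SD of a change over 3 years. The factor of 3 between the scales enters the sample size squared, so the choice of reading changes the answer ninefold.

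Two things depend on it. First, 1.64 dB is the assumption against which observed variability would be checked. Someone taking the label literally would compare the observed SD of the 3-year change with 1.64 dB, whereas the figure that supports 1,800 is about three times larger. Second, the reading decides how much room the trial has. On the literal reading, loss to follow-up hardly matters. On the annual reading, power sits just above 80% with nothing set aside for losses.

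**Working it through.** **Inputs from the power paragraph:** total 1,800; power 80%; annual means 0.86 and 0.64 dB; SD 1.64 dB.

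**Assumed, because the paragraph does not state them:** two-sided alpha 0.05; 1:1 allocation, so 900 per arm; a two-sample comparison of means with the normal approximation.

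**Formulas.** With difference d and standard deviation SD:
- n per arm = 2 × (1.96 + 0.8416)² × SD² / d² = 15.70 × (SD/d)², rounded up.
- Power at 900 per arm = Φ(d / [SD × √(2/900)] − 1.96).

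**1. The reading that reproduces the protocol's figure: both on the annual scale.** d = 0.22 and SD = 1.64.
- n = 15.70 × (1.64/0.22)² = 15.70 × 55.57 = 872.3, so 873 per arm and 1,746 in total.
- At 1,800: 0.22 / (1.64 × 0.04714) = 2.85, which gives 81.2% power.

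**2. The SD as labelled: both on the 3-year scale.** d = 3 × 0.22 = 0.66 and SD = 1.64.
- n = 15.70 × (1.64/0.66)² = 15.70 × 6.17 = 96.9, so 97 per arm and 194 in total.
- At 1,800: 0.66 / (1.64 × 0.04714) = 8.54, which gives power above 99.9%.
- Difference detectable with 80% power at 1,800: 2.8016 × 1.64 × 0.04714 = 0.217 dB over 3 years, or 0.072 dB per year.

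**3. In between: 1.64 as the SD of a single-year change, with independent yearly increments.** The 3-year SD is 1.64 × √3 = 2.84. With d = 0.66 this gives 291 per arm, 582 in total, and 99.9% power at 1,800. This does not reproduce the figure either.

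**4. The SD that would be needed.** For exactly 80% power at 1,800 with d = 0.66, the SD of the 3-year change must be 0.66 / (2.8016 × 0.04714) = 5.00 dB, about three times the printed value.

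**5. Can other design choices rescue the label?** Totals on the literal 3-year scale:

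| Variant | Total N |
|---|---|
| One-sided 0.05, 80% power | 154 |
| Two-sided 0.05, 90% power | 260 |
| 2:1 or 3:1 allocation | 219 or 260 |
| Inflated for 30% loss | 278 |
| Two-sided 0.001, 90% power | 518 |

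None comes near 1,800. The ratio between readings 1 and 2 is (0.66/0.22)² = 9 before rounding, whatever the alpha or allocation. The match in reading 1 does depend on alpha: one-sided 0.05 at 80% power would give 1,376.

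**6. Margin on the annual reading.** With assumed losses of 5%, 10% or 20% from 1,800 (the Protocol gives no figure), power based on completers is about 79%, 77% or 72%.

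**The case against.** The best defence is that the parenthesis is loose wording for the SD of annual changes as estimated over 3 years of follow-up. The sentence is about annual increases, so this is a natural reading, and on it the sample size and the 80% claim both stand, slightly on the safe side. That is a fair account of how the sentence may have arisen, but the printed words still attach 1.64 dB to changes over 3 years, and no source is given that would settle it.

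The planned mixed model does not rescue the label. If time is linear in years, the interaction is a difference in annual slopes, for which the matching variability is that of annual rates. Repeated visits and baseline adjustment would generally lower the required number, moving the literal reading further from 1,800.

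A reader might also infer more than the document supports:
- **That the trial is about nine times too large, or that its power is wrong.** This follows only if 1.64 dB truly is a 3-year SD.
- **That the sponsor did compute with an annual SD.** The calculation is not shown. The match at 1,746 makes this plausible but does not prove it.
- **That the 3-year SD is exactly 4.92 dB.** 3 × 1.64 = 4.92 holds if the rate is the Year 3 minus baseline change divided by 3. If 1.64 dB is the SD of slopes fitted to four visits, measurement error with variance s² adds s²/5 to the slope variance, against 2s²/9 for the endpoint rate. The implied 3-year SD then lies between 4.92 dB (no measurement error) and 5.19 dB (all measurement error).
- **That a null result could not be interpreted.** It would be read from the confidence interval for the treatment-by-time interaction, which does not use the planning SD.

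**Conclusion.** The point holds as a contradiction within the power statement: the printed inputs, as labelled, do not give the printed result. Either the SD label is wrong and 1,800 with 80% power stands (81.2% by this check), or the label is right and the stated power and detectable difference are wrong (above 99.9%, and about 0.07 rather than 0.22 dB per year). The document alone cannot decide between them. The individual figures rest on the assumed two-sided 0.05 and 1:1 allocation. The ninefold gap does not.

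**What to change.** Confirm where 1.64 dB comes from and state the difference and the SD on the same time scale.

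- **If it is the SD of individual annual rates:** relabel it as 1.64 dB HL per year. If a 3-year equivalent is wanted, give about 4.9 dB and say that it assumes the rate is the Year 3 minus baseline change divided by 3. The sample size and power then stand.
- **If it is the SD of the 3-year change:** restate the power and the detectable difference for 1,800.

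In either case, state the alpha, its sidedness and the allocation ratio used. The cost is a sentence or two in the Protocol. Enrolment need not change.

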## 3) Hearing threshold will correlate inversely with cognitive function.

- Hearing threshold at baseline will correlate inversely with cognitive function at baseline.
- The trajectory of change in hearing threshold from baseline through to Year 3 will correlate with the trajectory of cognitive change across the study.
- Slowing of rate of change in hearing threshold in the aspirin group will be associated with greater preservation of cognitive function.

*The basis of this hypothesis is that age related decreases in cognition and hearing may share a common pathogenesis, possibly due to low-grade inflammation and/or microvascular change. If so, it might be expected that both cognition and hearing would decline in parallel. Furthermore, if hearing loss directly contributes to cognitive decline via reduction of stimuli including social interaction, both might also decline in parallel.*

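### No planned model estimates the course of 3MS by arm or jointly with hearing, so the third part of subsidiary hypothesis 3 is untested and the promise of causal relationships is unsupported

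*Protocol*

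**What the plan says.** Protocol, Statistical Analysis, fixes the outcome: "A linear mixed model with HL at years 0, 1, 2, and 3 as the repeatedly measured outcome will be used for all analyses". It extends this to the subsidiary hypotheses ("The same model structure will be used to assess evidence for the subsidiary hypotheses") and includes cognition in the list: "for cognitive impairment as measured by 3MS noting that each of these measures is on a continuous scale".

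The steps are worked through for TNF-alpha. Its baseline value is added first. Then "the model will be further extended to include the time-dependent TNF- $\alpha$ change from baseline as an explanatory variable". For mediation, "the model will be extended again to include an interaction between treatment group (placebo/aspirin) and the time-dependent TNF- $\alpha$ change from baseline".

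Subsidiary hypothesis 3 has three parts. The first is an inverse correlation of hearing threshold and cognition at baseline. The second is a correlation of their trajectories to Year 3. The third is: "Slowing of rate of change in hearing threshold in the aspirin group will be associated with greater preservation of cognitive function". The rationale offers a shared pathogenesis and, as a further possibility, "if hearing loss directly contributes to cognitive decline via reduction of stimuli including social interaction, both might also decline in parallel".

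Section 5, Cognitive Function Tests, says that "results from annual cognitive function assessments will allow determination of associations and causal relationships" by comparing annual changes. It adds a Year 2 3MS to the parent trial's Years 0, 1 and 3, so that 3MS is annual.

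**The concern.** The third part of hypothesis 3 is about what happens to cognition when aspirin slows hearing loss. To assess it, the analysis must describe the course of 3MS, either by arm or jointly with HL. If HL is the outcome throughout, 3MS is always on the right-hand side and its own course is never estimated.

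The last extension does not fill the gap. A treatment by 3MS-change term with HL as outcome measures whether the HL-3MS association is stronger in one arm than in the other. That is effect modification. It does not say whether cognition was better preserved on aspirin, or whether any preservation went with slower hearing loss.

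At stake is one part of one subsidiary hypothesis. The trial could collect annual 3MS, including a measure added for this purpose, and report an interaction p-value that does not bear on the question. The causal wording in section 5 invites readers to take a same-visit association as evidence of direction.

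**Working it through.** **1. The plan's own figure.** The only sample-size figure is for the main hypothesis. The difference is 0.86 − 0.64 = 0.22 dB per year and the SD is 1.64. Assuming two-sided 5% and 1:1 allocation, n per arm = 2 × (1.96 + 0.84)² × 1.64² / 0.22² ≈ 873, or 1,746 in total. With 900 per arm, power is 81.2%. This agrees with the stated 1,800 and 80%. It concerns HL alone; no figure is given for hypothesis 3. (Whether that SD belongs with an annual difference is a separate question that does not affect this point.)

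**2. Each part of hypothesis 3 against the planned term.**

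| Part | What it claims | Planned term (outcome HL) | Answered? |
|---|---|---|---|
| First | Baseline correlation | Baseline 3MS | Yes; correlation is symmetric |
| Second | Correlation of trajectories | 3MS change from baseline | Yes, as association |
| Third | Slower hearing loss on aspirin goes with preserved cognition | Treatment × 3MS change | No |

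**3. Why the interaction misses the third part.** Within an arm, once the mean course is removed, the coefficient of 3MS change is Cov(HL change, 3MS change) / Var(3MS change). The interaction is the difference of this ratio between arms. A treatment that shifts mean HL and mean 3MS but leaves variances and covariance alike gives an interaction of zero, however large the shifts. The third part is a statement about those shifts.

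**4. Illustration.** 1,800 participants, 1:1, changes from baseline at Years 1 to 3, 300 runs per scenario, regression with participant-clustered errors as a simple stand-in for the mixed model. From the Protocol: an aspirin effect of 0.22 dB per year on hearing. Assumed, not in the documents: slope SD 1 (residual SD 1 where one slope drives the other) and measurement SD 2 on both scales, and the strength of the hearing-cognition link. The association is the same in both arms in every scenario.

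| Scenario | Assumed strength | 3MS-change coefficient (significant) | Treatment × 3MS change significant | Aspirin effect on 3MS per year, 3MS as outcome (significant) |
|---|---|---|---|---|
| Hearing drives cognition | 0.25 | −0.130 (100%) | 6.3% | 0.052 (17%) |
| | 0.5 | −0.239 (100%) | 6.3% | 0.110 (47%) |
| | 1.0 | −0.351 (100%) | 3.3% | 0.217 (86%) |
| Cognition drives hearing | 0.25 | −0.133 (100%) | 5.7% | 0.876 (100%) |
| | 0.5 | −0.270 (100%) | 3.7% | 0.440 (100%) |
| | 1.0 | −0.538 (100%) | 4.7% | 0.221 (99%) |
| Common cause; aspirin acts on hearing only | 0.25 | −0.120 (100%) | 6.3% | 0.000 (4%) |
| | 0.5 | −0.212 (100%) | 4.7% | −0.001 (5%) |

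The Monte Carlo standard error near 5% is √(0.05 × 0.95 / 300) ≈ 1.3 percentage points, so the interaction column is compatible with 5% throughout. When hearing drives cognition, the true effects on 3MS are 0.22 × 0.25 = 0.055, 0.22 × 0.5 = 0.11 and 0.22 × 1.0 = 0.22, and the 3MS-outcome model recovers them.

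Two readings follow. The interaction looks the same whether cognition is preserved (first two scenarios) or not (third), while the 3MS-outcome model separates them. The association coefficient is negative and always significant under all three causal structures, so it cannot order hearing and cognition.

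**5. Data already scheduled.** 4 visits × 1,800 = 7,200 HL-3MS pairs. For a model of 3MS on HL at the previous visit, Year 0 drops out: 3 × 1,800 = 5,400 pairs. Both counts are maxima before dropout.

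**The case against.** The strongest reply is that hypothesis 3 is worded as correlation and association. Regressing HL on 3MS is a valid test of a correlation, and the shared-pathogenesis rationale has no direction. This stands for the first two parts. A reader might infer that the whole hypothesis is modelled in reverse; the documents do not support that. The Background section on hearing loss and cognitive decline also cites a cohort in which probable cognitive impairment predicted faster hearing decline, so HL as outcome matches part of the cited evidence. The same section cites hearing loss as a predictor of dementia and of accelerated cognitive decline, a direction that the analysis leaves out.

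Second, no part of the hypothesis states on its own that aspirin preserves cognition, and dementia belongs to the parent trial's primary outcome. This also stands: the plan does not break a free-standing promise on aspirin and cognition. But the third part links slowed hearing loss to preserved cognition in this cohort, and even as an association it needs a cognitive trajectory.

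Third, the interaction fails even where cognition drives hearing. Reversed direction is therefore not the cause. A treatment by intermediate-variable interaction does not by itself test mediation, and the same caution applies to hypotheses 1 and 2. The mediation wording is given only for TNF-alpha, so a reader who says that the plan calls 3MS a mediator of hearing loss is extrapolating.

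Fourth, details may be left to a statistical analysis plan, which is not at hand. How the extensions are adapted to 3MS could be such a detail. The choice of HL as outcome for all analyses is not: the Protocol states it.

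**Conclusion.** The point holds in a limited form. The planned model serves the two association parts of hypothesis 3. The third part has no test, because no stated model estimates 3MS over time by arm or jointly with HL. The causal wording in section 5 goes beyond what the stated analysis can show.

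The first conclusion rests on the Protocol's text and on what an interaction coefficient measures, not on the simulation. The simulated percentages depend on assumed variances and link strengths and on an association that is equal in both arms. They illustrate and do not predict this trial's power. The primary analysis and the data collection are unaffected. This is a cheap improvement, not a flaw in the trial's main conclusion.

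**What to change.** - **3MS as outcome.** For the third part, add a linear mixed model with 3MS at Years 0 to 3 as outcome and a treatment by time term. Do not include post-randomisation HL in it: on a path from aspirin through hearing to cognition, that would adjust away the effect of interest.
- **Joint model.** Add a bivariate mixed model for HL and 3MS. Report the treatment effect on each slope and the correlation of the slopes. This addresses the third part directly and also serves the second.
- **Temporal order, if wanted.** Fit a separate model of 3MS at Years 1 to 3 on HL at the previous visit (at most 5,400 pairs at 1,800 participants), reported as association. The lag helps with order but does not establish cause.
- **Wording.** In section 5, keep associations and delete causal relationships. In Statistical Analysis, limit the statement that HL is the outcome of all analyses so that it allows these models.

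The cost is a few sentences and a few more secondary analyses on data already scheduled. The downside is modest power for any aspirin effect on 3MS: as low as 17% in the weakest case illustrated where hearing drives cognition. Estimates with confidence intervals should therefore be reported, and a null result should not be read as absence of effect.
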